##### Fitbit flex

Following the education and training session, participants will be asked to wear the Fitbit 24 h/day (unless charging) for the remainder of the study. The Fitbit Flex is a removable tracker (housing a triaxial accelerometer and five-light LED display) inside of a wristband worn on the non-dominant wrist. The Fitbit user-interface is an easy-to-use web-based application that graphically displays a user’s activities over the course of the day including total steps taken, calories burned, and distance traveled. Interaction with the user-interface may occur on a self-directed basis.

##### Telephone follow-up

Participants will be asked to share their Fitbit activity data with the physiotherapist they work with during the education session. This is accomplished using Fitbit’s online social networking function where users can privately share Fitbit activity “profile” with Fitbit “Friends”. Participants add the physiotherapist as a “Friend”, thus allowing the physiotherapist to view the participant’s activity data. These data will be used to inform the content of a 20-min weekly phone call to each participant from the physiotherapist (for the first 4 weeks of the intervention only). Like the goal setting portion of the education session, these conversations are derived from a Brief Action Planning protocol and are designed to respect participant autonomy while increasing confidence in PA participation. Furthermore, the physiotherapist may be contacted by email to address participant questions throughout the duration of the intervention as they arise.

#### Risk management and safety monitoring

Adverse events during the study will be tracked both by self-report on the online outcome measure questionnaire and by study physiotherapists during follow-up phone calls. In the online questionnaire, participants are asked if they experienced any negative outcomes (presented as a list of outcomes and allowing for free form entry at the end of the questionnaire) as a result of becoming more physically active since their enrollment in the study. They are asked to specify when the event occurred and if the event was experienced before. In an open-format response, participants are asked to describe the symptoms they experienced, any medical help they sought as a result, and any other relevant information. Any participants reporting adverse events will be immediately contacted and, if necessary, assessed by a study physiotherapist before being referred for appropriate care as needed.

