#### Feasibility data

To address the primary objective, data relating to trial feasibility will be collected. As suggested by Thabane et al. [36], these data will be been organized according to process, resources, management, and scientific issues. Setting benchmarks for feasibility data is beneficial to inform larger-scale assessments of this intervention in the future [36]. Thus, benchmark criteria for success were set in accordance with the goals of an upcoming proof-of-concept study featuring the present intervention (see Table 2). Detailed information on the recruitment process will be collected, including the number of individuals who contacted us, the source of recruitment, and the reason for non-eligibility or withdrawal of interest. Adherence to study protocols (education and training session attendance, telephone follow-up, Fitbit use, outcome measure collection) will be assessed for each participant by determining whether a participant completed each component of the study. It has been determined that at least 4 days of data are required to obtain accurate estimates of PA participation from the SenseWear armband [37]. Time to complete online questionnaires will be collected from the online survey system. As the cost of activity monitors (Fitbit and SenseWear) in this study is a concern, extremely high equipment retention and reliability is required. Management issues such as unforeseen challenges with the host location, study personnel, or data collection that challenge study logistics or success will be carefully documented. Safety issues and adverse events will be tracked throughout the study (see “Risk management” subsection below). Feasibility data will be tracked and logged in a detailed administrative database and summarized for presentation at study completion. Treatment effect and variance estimates will be calculated in order to inform sample size calculations for the larger trial. These calculations will be carried out assuming a randomized trial with two equal-sized groups, a two tailed significance threshold (alpha) of 0.05, and power of 0.8 to detect a significant result between groups on bouted MVPA and sedentary time outcomes.

**Table 2 Tab2:** Feasibility data to be collected and criteria for success

Feasibility data category	Item of interest	Success criteria
Process	Recruitment rate	2 participants/week
	Consent rate	≥90 %
	Dropout rate	≤10 %

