	Adherence to protocols	4 days × 20 h for each SenseWear week; 100 % completion of online questionnaires; mean 5 days/week of Fitbit use
Resources	Equipment loss/reliability	100 % equipment retention
	Personnel	Sufficient personnel to execute the trial efficiently
Management	Location, logistics, personnel, data	No criteria set
Scientific	Intervention effect, variation, safety	No criteria set

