#### Assessments

Assessment of outcome measures will occur at three time points—baseline (T0), week 5 (T1), and week 10 (T2)—with the exception of demographic information (collected at baseline only) and adverse events (collected at T1 and T2 only). Both the KOOS and PIH will be uploaded to an online survey system hosted on a secure local server at Arthritis Research Canada, and the SenseWear armbands will be delivered to participants prior to each data collection week.

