#### Randomization

Once informed consent is received and baseline measures have been collected, participants will be randomly assigned to one of two groups (immediate-intervention group or delayed intervention group). As per the stepped-wedge design, the delayed-intervention group will receive the intervention after a 5-week waiting period (i.e. immediately following T1 follow-up assessment; see Fig. 2). A study statistician ([name]) not involved in the day-to-day operation of the trial will randomly assign participants in blocks to each group using a computer-based random number generator and a 1:1 allocation ratio. Block sizes will be concealed from study staff and randomly varied to prevent prediction of group allocation. The statistician will pass group allocations back to study research coordinators (CC, NG) who will arrange for intervention delivery as appropriate. Group assignments will be accessible only to the study research coordinators.

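### Adverse events are sought by weekly calls only while the intervention is delivered, and by a question tied to increased activity, so any comparison with waiting time would be open to ascertainment bias

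*Protocol article*

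**What the plan says.** Three sections of the protocol article describe adverse event collection.

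- *Risk management and safety monitoring*: events are "tracked both by self-report on the online outcome measure questionnaire and by study physiotherapists during follow-up phone calls". The questionnaire item covers negative outcomes "as a result of becoming more physically active since their enrollment in the study". It offers a list of outcomes and free-form entry. On timing: "They are asked to specify when the event occurred and if the event was experienced before".
- *Assessments*: in a sentence that schedules the outcome measures at baseline, week 5 and week 10, one listed exception is "adverse events (collected at T1 and T2 only".
- *Feasibility data*: "Safety issues and adverse events will be tracked throughout the study". In Table 2, safety appears in the row "Intervention effect, variation, safety", for which no success criterion is set.

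Two other sections fix who is called and when. Under *Telephone follow-up* the weekly calls are made "for the first 4 weeks of the intervention only". Under *Randomization*, "the delayed-intervention group will receive the intervention after a 5-week waiting period", that is, directly after the week-5 assessment.

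**The concern.** Weeks 0-5 are the only period with a randomised untreated comparator. In that period one group is in weekly contact with a clinician who records adverse events and the other is not. The one shared instrument asks participants to report only harms that they themselves put down to increased activity. Someone still waiting for the programme has little reason to count a knee flare or a fall under that heading. Both features push recorded events in waiting time downwards relative to intervention time.

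Safety is a listed scientific item of this pilot, which is meant to inform a larger trial. If event counts are set side by side by group at week 5, or before and after the programme in the delayed group, part or all of any excess under the intervention could come from how events were sought.

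**Working it through.** The document gives no adverse event rate, so there is no figure of its own to reproduce. Two checks are possible.

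**1. Scheduled reporting contacts**

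Inputs: one call a week for the first four weeks of the intervention, giving 4 calls (*Telephone follow-up*); one questionnaire at week 5 and one at week 10 (*Assessments*); delayed start after the week-5 assessment (*Randomization*).

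| Period | Immediate group | Delayed group |
|---|---|---|
| Weeks 0-5 | 4 + 1 = 5 | 0 + 1 = 1 |
| Weeks 5-10 | 0 + 1 = 1 | 4 + 1 = 5 |
| Whole study | 6 | 6 |

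The totals balance by group but not by exposure: all calls fall after the intervention has started and none in waiting time.

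**2. What unequal contact could do when true risks are equal**

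All capture rates here are assumptions. Let q be the chance that the questionnaire captures an event and c the chance that any one call does, with independent capture. Then:

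- observed risk with calls = true risk × [1 − (1 − q)(1 − c)^4]
- observed risk without calls = true risk × q
- apparent ratio = [1 − (1 − q)(1 − c)^4] / q, in which the true risk cancels

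Example with q = 0.5 and c = 0.1: (1 − 0.5 × 0.6561) / 0.5 = 0.672 / 0.5 = 1.34.

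| q | c = 0 | c = 0.1 | c = 0.2 | c = 0.3 |
|---|---|---|---|---|
| 0.3 | 1.0 | 1.80 | 2.38 | 2.77 |
| 0.5 | 1.0 | 1.34 | 1.59 | 1.76 |
| 0.7 | 1.0 | 1.15 | 1.25 | 1.33 |
| 0.9 | 1.0 | 1.04 | 1.07 | 1.08 |

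In counts, with 18 per group (36 at 1:1) and an assumed true risk of 20%, the row q = 0.5 gives 18 × 0.2 × 0.5 = 1.8 events without calls. With calls it gives about 2.4 (c = 0.1) to 3.2 (c = 0.3).

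The table uses the same q in both groups. The item's wording would be expected to lower q in the waiting group, which widens the gap; that effect is not modelled.

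**3. Wording on timing**

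Read literally, collection at T1 and T2 only cannot stand beside weekly calls or tracking throughout the study.

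**The case against.** The strongest reply is that no biased comparison is planned. The *Statistical analysis* section models bouted MVPA, bouted sedentary time, KOOS and PIH; adverse events are not among them, and Table 2 sets no safety criterion. This stands. A reader might infer that the trial's safety comparison is biased, or that an excess of events will appear. The document supports neither: it states no such comparison, and the ratio is exactly 1.0 if calls detect nothing extra.

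Other replies also carry weight:

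- A reader might see a flat contradiction over timing. The *Assessments* sentence lists exceptions to the three-visit schedule and can be read as meaning not at baseline. *Risk management and safety monitoring* names both sources plainly. What remains is loose wording.
- A reader might infer that waiting participants cannot report events. The list and free-form entry leave room to do so, and the article may be paraphrasing the item. The wording discourages reporting; it does not block it.
- Recall runs from enrolment at both follow-ups, which suggests double counting. Because participants are asked when each event occurred, events can largely be assigned to a period and duplicates found.
- KOOS measures knee pain and symptoms identically in both groups at all three time points, so average worsening is compared symmetrically. It does not count individual events or falls.
- The article does not say that the larger trial needs a background event rate; its planned sample-size work concerns MVPA and sedentary time.

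None of this removes the unequal contact schedule or the attribution built into the shared question.

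**Conclusion.** The point holds in a conditional form. Scheduled contacts in weeks 0-5 are 5 versus 1, and the shared item is likely to under-count events in people still waiting. Three summaries would therefore be open to ascertainment bias: a week-5 contrast between groups, a before/after contrast in the delayed group, and a background rate from waiting time. The direction, towards the intervention looking less safe, follows if calls detect anything extra or if the wording deters waiting participants from reporting.

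The size cannot be taken from the document. The range of 1.0 to 2.77 in the table rests wholly on assumed, independent capture rates. In a 36-person pilot with no planned adverse event test this is a modest issue. It is worth correcting because safety is a listed feasibility item and the correction is cheap. The timing statements are a wording inconsistency.

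**What to change.** 1. Reconcile *Assessments*, *Feasibility data* and *Risk management and safety monitoring* into one adverse event schedule that names both sources and says when each applies.
2. Ask both groups the same neutral question about any new or worsened problem, and record attribution to activity in a separate item.
3. Base any between-group or waiting-versus-intervention safety summary on questionnaire events only, and list call-reported events separately.

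The cost is one edited online item and some reporting text. The article reports 34 of 36 participants already recruited, so the new wording mainly helps the remaining assessments and the larger trial. Participants already assessed have answered the existing item, and results must be reported by item version. Tabulation by source can be adopted for everyone. On its own it removes the call imbalance but not the effect of the existing wording, so questionnaire counts from waiting time collected with that wording still need a caveat.

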#### Data management

Data will be stored in confidential servers on the Arthritis Research Canada premises. Participant ID’s are assigned upon enrollment, with a secondary ID assigned upon randomization. To ensure anonymity, participants are referred to by their study ID in emails and verbal communications where necessary. Access to all computer files with participant information will be limited to the study team, and individual files will be password protected. SenseWear data will be downloaded by a staff member (JY), who is blinded to participant’s group assignment, using SenseWear Professional Software 8.0, and exported to Excel (Microsoft, Redmond, WA) and processed in MatLab (The MathWorks, Inc., Natick, MA, USA). Data quality will be monitored on an ongoing basis by study staff, and backups will be saved weekly. The final de-identified data set will be provided to a blinded study statistician for analysis.

#### Sample size calculation

As pilot studies are primarily concerned with feasibility and generating estimates that will inform future studies’ power and sample size calculations, sample size, or power calculations were not deemed necessary for this trial [47]. A convenience sample of 36 participants was estimated to allow sufficient piloting of study protocols and estimates of feasibility measures to inform a future trial.

#### Statistical analysis

Descriptive measures will be tabulated and summarized by count, percentage, or mean, and 95 % CI and compared for differences between groups. Integrity of the randomization process will be monitored. SenseWear armband measurements for each time point will be considered valid if they include at least 4 days with at least 20 h of wear time each day [50]. Feasibility data will be collated and compared against benchmarks for success. When assessing preliminary intervention efficacy, the stepped-wedge design allows for analyses of differences between groups as well as temporal patterns. Changes in bouted MVPA, bouted sedentary time, KOOS score, and PIH score will assessed by a multiple regression model including variables for group, time, and group-time interaction. The effect of blocking will be considered in the analysis. Planned comparisons will be used to compare group means for differences at first follow-up (week 5) and to test for a delay effect and for temporal changes intervention efficacy. All analyses will be conducted using IBM SPSS Version 20 (Armonk, NY, USA).

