**Methods/design:**

Thirty-six participants will be recruited from the community for a two-group pilot randomized controlled trial with a stepped-wedge design using an intention-to-treat analysis. Computer-generated block randomization will be performed using varying block sizes and a 1:1 allocation ratio. The 4-week intervention will be delivered immediately (immediate-intervention group) or after a 5-week delay (delayed-intervention group). Outcome measures of pain and disability (Knee Injury and OA Outcome Score), disease self-management ability (Partners in Health Scale), and objective bouted moderate-to-vigorous PA and sedentary time (BodyMedia SenseWear Mini Armband) will be collected at baseline (week 0) and two follow-ups (weeks 5 and 10), for a total study duration of 11 weeks. Feasibility data relating to process, resource, management, and scientific elements of the trial will be collected. Outcome measure and feasibility data will be summarized, and an estimate of intervention efficacy will be obtained by regression model with planned comparisons. The trial began recruiting in February 2015. To date, 34 subjects have been recruited.

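### The efficacy regression on group, time and group-time has no term for within-participant correlation, so if fitted as written its temporal contrasts get wrong standard errors

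*Protocol article*

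**What the plan says.** Under Assessments, the protocol article states: "Assessment of outcome measures will occur at three time points". These are baseline (T0), week 5 (T1) and week 10 (T2), all on the same people. The Sample size calculation section sets the number: "A convenience sample of 36 participants was estimated to allow sufficient piloting of study protocols". Under Randomization they are allocated "using a computer-based random number generator and a 1:1 allocation ratio", which means about 18 per group.

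The efficacy model is in the Statistical analysis section, where changes in the four outcomes are to be "assessed by a multiple regression model including variables for group, time, and group-time interaction". The next sentence names one further design feature: "The effect of blocking will be considered in the analysis". The comparisons follow: "Planned comparisons will be used to compare group means for differences at first follow-up (week 5", together with tests for a delay effect and for change in efficacy over time. The abstract also mentions only a regression model with planned comparisons.

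The article names no participant effect, mixed model, repeated-measures covariance, generalised estimating equations or clustered standard errors. Nor does it say whether the modelled outcome is the level at each visit or the change from baseline.

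**The concern.** Because time and group-time are in the model, each participant must supply more than one row. Rows from one person are correlated, and the listed terms do not account for that. Ordinary regression on those terms uses one pooled residual variance for every contrast, although contrasts within a person and contrasts between people have different true variances.

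The article justifies the stepped-wedge design partly by the temporal patterns it allows. The delayed group's response to treatment is itself a within-person change from week 5 to week 10, so these contrasts depend directly on how the repeated measurements are handled. The Feasibility data section also says that effect and variance estimates from this pilot will inform the sample size of the larger trial.

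**Working it through.** **Inputs.** 36 participants at 1:1, so 18 per group (Sample size calculation; Randomization). Three visits (Assessments). The article gives no power or sample-size figure for this trial, so there is no plan figure to reproduce. The within-person correlation ρ is not given either. It is assumed equal between all pairs of visits and is varied from 0.3 to 0.8. Variances are assumed equal across visits, and time is taken as a three-level factor.

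**Reading 1: levels at all three visits.** There are 36 × 3 = 108 rows and 6 cell means, leaving 102 residual degrees of freedom. The residual variance estimates the between-person variance σ² at one visit.

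- Week-5 group difference: the true variance is 2σ²/18 and ordinary least squares (OLS) also gives 2σ²/18. The ratio of standard errors is 1.
- Within-arm change: true 2σ²(1−ρ)/18, OLS 2σ²/18. The ratio of standard errors is 1/√(1−ρ).
- Group-time contrast (difference between arms in change): true 4σ²(1−ρ)/18, OLS 4σ²/18. The ratio is again 1/√(1−ρ).

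The true type I error of a nominal 5% test is 2[1 − Φ(1.96 × ratio)]:

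| ρ (assumed) | OLS SE / true SE for change and group-time | True type I error | Variance of change overstated by 1/(1−ρ) |
|---|---|---|---|
| 0.3 | 1.20 | 1.9% | 1.43 |
| 0.5 | 1.41 | 0.6% | 2.00 |
| 0.7 | 1.83 | <0.1% | 3.33 |
| 0.8 | 2.24 | <0.1% | 5.00 |

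Simulation of 20,000 trials per ρ agrees. SE ratios for the group-time contrast were 1.20, 1.42, 1.81 and 2.23. For the delayed arm's T1-to-T2 change they were 1.19, 1.40, 1.82 and 2.22. The week-5 group difference had ratios of 0.99 to 1.00 and type I error of 4.9% to 5.4%.

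The loss of power can be illustrated with a within-arm change of 0.45 SD. That size is an assumption, not a figure the article gives for this contrast. Power as written is about 19% at ρ = 0.5 and 11% at ρ = 0.8, against about 44% and 83% for a paired analysis (simulated, good to about two percentage points).

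**Reading 2: change scores at T1 and T2, stacked.** Both changes subtract the same baseline. Their covariance is σ²(1−ρ) and each has variance 2σ²(1−ρ), so their correlation is 0.5 whatever ρ is.

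- Group effect averaged over the two changes: OLS SE / true SE = 1/√(1 + 0.5) = 0.82. Type I error is 2[1 − Φ(1.96 × 0.82)], about 11%.
- Difference between the T2 and T1 changes: ratio 1/√(1 − 0.5) = 1.41, so conservative.
- Group difference in change at week 5 alone: one row per person, ratio 1.

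**Delay effect.** The article does not define it. If it compares the immediate group at T1 with the delayed group at T2, the two means come from different people and the levels model gives the right standard error. If it compares each group's own change over its treatment period, the ratio is 1/√(1−ρ), as in the table.

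**Planning variance.** On reading 1 the residual variance is σ², which implies a variance of change of 2σ². The true value is 2σ²(1−ρ), so the implied figure is too large by 1/(1−ρ), the last column of the table. For a future comparison of unadjusted follow-up levels, σ² is the right input.

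**The case against.** The strongest objection is that the sentence lists explanatory variables and is silent on the error structure. Multiple regression may be loose wording for a repeated-measures model, and a journal article commonly leaves covariance structure to a fuller plan that is not shown here. That stands as a limit: the article does not say that rows are treated as independent, and a reader who concludes that they will be is inferring it. It does not remove the point. The article names a method and its terms, adds blocking as a further feature, and the method as named does not suit repeated measurements on either reading of the outcome.

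Three stronger readings are tempting and are not supported.

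- A reader might infer that every planned p-value and interval is wrong. The week-5 group comparison, the only fully specified one, has a correct standard error.
- A reader might infer large false-positive rates on the levels reading. A group effect averaged over all three visits would have type I error of about 12% to 22% for ρ from 0.3 to 0.8, since its SE ratio is 1/√(1+2ρ). The article plans no such contrast, and it would mean little here: baseline precedes randomization, and by week 10 both groups have been treated.
- A reader might see a conflict with the abstract's statement that the trial is "using an intention-to-treat analysis". There is none: stacked OLS also uses every participant with at least one valid measurement.

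It is also fair that the article does not say the planning variance will come from this regression, or that the larger trial will analyse change. The variance argument is therefore conditional.

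**Conclusion.** The point holds with limits. Fitted as written to visit levels, the model overstates the standard errors of within-arm change and group-time contrasts by a factor of about 1.2 to 2.2, which is conservative and wastes power. On the stacked-change reading, temporal contrasts are again conservative, while a group effect averaged over the two follow-ups is anti-conservative, at about 11%. The week-5 comparison is sound on both readings, and the delay effect depends on its definition. The planning variance is overstated by 1.4 to 5 times only if it is derived from the levels residual and used for an analysis of change.

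These sizes rest on equal within-person correlation of 0.3 to 0.8, equal variances and complete data. None of these is given in the article. The importance is moderate: preliminary efficacy is among the primary objectives, but this is a pilot with a convenience sample and no power claim.

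**What to change.** In the Statistical analysis section, replace the multiple regression with a linear mixed model for repeated measures. It should have time as a three-level factor, group, group-by-time, a participant random intercept or an unstructured covariance, and small-sample degrees of freedom (Satterthwaite or Kenward-Roger, as the software allows). Take the week-5, delay and temporal comparisons as contrasts from that model. State whether levels or changes are modelled, and define the delay effect as a contrast. For planning the larger trial, report the within-person correlation or the variance of change beside the between-person variance.

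For the week-5 comparison alone, a baseline-adjusted analysis at that visit would also avoid the problem, but it would not cover the temporal contrasts. The cost is one sentence of analysis wording and a different SPSS procedure. No new data are needed.

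### The week-5 efficacy comparison should be stated as baseline-adjusted: the model described does not include the pre-randomisation value as a covariate

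*Protocol article*

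**What the plan says.** The Statistical analysis section of the protocol article says that changes in the four outcomes (bouted MVPA, bouted sedentary time, KOOS and PIH) will be assessed by a multiple regression with terms for group, time and their interaction, and that blocking will be considered. It continues: "Planned comparisons will be used to compare group means for differences at first follow-up (week 5". No baseline covariate is listed, and nothing says that the week-5 comparison is or is not adjusted for baseline.

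The baseline values exist before allocation. The Randomization section states: "Once informed consent is received and baseline measures have been collected, participants will be randomly assigned to one of two groups". The Assessments section places the outcome measures at T0, T1 (week 5) and T2 (week 10). The delayed group starts the intervention directly after T1, so week 5 is the only visit at which a treated group is compared with one not yet treated.

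On size, the Sample size calculation section says: "A convenience sample of 36 participants was estimated to allow sufficient piloting of study protocols", and that "sample size, or power calculations were not deemed necessary for this trial". On the use of the results, the Feasibility data section says: "Treatment effect and variance estimates will be calculated in order to inform sample size calculations for the larger trial".

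**The concern.** The week-5 difference is the randomised estimate of efficacy. Measurements of the same outcome on the same person five weeks apart will normally be correlated, so the T0 value carries information about the T1 value. An analysis that does not estimate and use that relation gives a less precise estimate than the collected data allow. It also leaves the estimate exposed to whatever difference at baseline arises by chance with about 18 people per arm.

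The precision matters because the estimate has a use beyond this pilot: its effect and variance are inputs to the size of the next trial. The wording also leaves two analyses open, one on outcome levels and one on changes, and these can give different estimates from the same data.

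**Working it through.** **Inputs from the protocol article.** Total of 36 (Sample size calculation), allocated "using a computer-based random number generator and a 1:1 allocation ratio" (Randomization). This gives about 18 per arm; varying blocks make 18/18 expected but not certain. There is no power or precision figure for this pilot to reproduce.

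**Assumptions.** The T0–T1 correlation, rho, is not in the document; I take 0.3, 0.5, 0.7 and 0.8. The SD is taken as equal at T0 and T1, data are complete, and results are in SD units.

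**Step 1: what the described model estimates.** I fitted group, time and their interaction to one simulated complete data set (36 people, three visits, rho 0.7), by ordinary least squares and by a random-intercept mixed model. The week-5 group contrast was -0.0434 in both, equal to the raw difference in week-5 means. The T0-to-T1 interaction (least-squares fit) was 0.1466, equal to the difference in mean change. So including T0 as a time level does not adjust the week-5 contrast. The interaction does use baseline, but with its coefficient fixed at 1.

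**Step 2: standard error of the week-5 difference, 18 per arm.**
- Raw means: sqrt(2/18) = 0.333.
- Change scores: sqrt(2/18) × sqrt(2 − 2·rho).
- ANCOVA: sqrt(2/18) × sqrt((1 − rho²)(1 + 1/32)), where 1/32 = 1/(36 − 4) is the cost of estimating the slope.

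| rho | Raw | Change score | ANCOVA | ANCOVA SE below raw | ANCOVA SE below change |
|---|---|---|---|---|---|
| 0.3 | 0.333 | 0.394 | 0.323 | 3% | 18% |
| 0.5 | 0.333 | 0.333 | 0.293 | 12% | 12% |
| 0.7 | 0.333 | 0.258 | 0.242 | 27% | 6% |
| 0.8 | 0.333 | 0.211 | 0.203 | 39% | 4% |

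Simulation with 4,000 trials per value agrees. At rho 0.7 the empirical SDs are 0.333, 0.255 and 0.238; at 0.3 they are 0.328, 0.391 and 0.320.

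**Step 3: variance saving, ignoring the slope cost.** Against the raw contrast it is rho²: 9%, 25%, 49%, 64%. Against change scores it is 1 − (1 − rho²)/(2 − 2·rho) = (1 − rho)/2: 35%, 25%, 15%, 10%.

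**Step 4: chance imbalance.** The difference in baseline means has SE sqrt(2/18) = 0.333 SD, so a difference beyond 0.33 SD arises in about 32% of such trials and beyond 0.5 SD in about 13%. Given a 0.333 SD imbalance, the expected raw week-5 difference moves by rho × 0.333 = 0.10, 0.17, 0.23 or 0.27 SD. This is the variance loss seen from another side: the raw variance 2/18 splits into rho² × 2/18 from baseline imbalance and (1 − rho²) × 2/18 from the rest.

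**Step 5: what it means for sizing the next trial.** As illustration only, take the effect size of 0.45 from the 2008 meta-analysis in the Background, with "a two tailed significance threshold (alpha) of 0.05, and power of 0.8" from the Feasibility data section. The normal approximation gives 78 per arm for raw means. Multiplying the variance by 1 − rho² gives 71, 59, 40 or 28 per arm for an adjusted analysis. The spread shows why the residual SD and rho should be reported.

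**The case against.** The strongest case against has four parts.

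First, a reader might infer that the plan commits to an unadjusted comparison of raw means. The document does not say this. The model sentence speaks of changes in the outcomes and includes a group-by-time interaction, so baseline may enter as a change score or through the interaction. That stands: the wording is ambiguous, and the savings of 49% and 64% at rho 0.7 and 0.8 hold only on the raw reading. On the change-score reading they are 15% and 10%.

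Second, a reader might infer that chance imbalance biases the result. Under randomisation it does not. It is imprecision, already contained in the raw standard error, and not a second harm beside the variance loss.

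Third, the pilot was not sized for power, 0.45 is a background figure and not a design assumption, and rho is unknown. All of this stands, and it is why the size is given here as standard errors over a range of rho. The residual SD and rho could also be computed from the collected data however the contrast is worded.

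Fourth, this is a condensed article, and covariates may be left to an analysis plan that is not shown. The listed terms do not exclude a baseline covariate. However, the article does name its model terms and its week-5 contrast, so this is a stated method that can be improved and not merely an absent detail. Neither reading of that method is as precise as ANCOVA at any correlation examined, so the remedy does not depend on which reading was meant.

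**Conclusion.** The point holds in a limited form. As described, the model and the week-5 comparison do not use the pre-randomisation value as a covariate, and stating that they do would be better on either reading. With 18 per arm and rho from 0.3 to 0.8, ANCOVA lowers the standard error by 3% to 39% against raw means and by 18% down to 4% against change scores. At rho 0.5 the gain is 12% against both.

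The size rests on an assumed correlation, equal SDs at T0 and T1, and complete data. No figure in the protocol is wrong, and no power claim is affected. The consequence falls on the precision of the preliminary efficacy estimate and on the effect and variance carried into the larger trial. It is a recommended improvement, not a flaw that invalidates the pilot.

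**What to change.** State in the Statistical analysis section that the week-5 efficacy estimate for each outcome is baseline-adjusted, and give its 95% CI. Either of two forms will do: an ANCOVA of the T1 value on group and the T0 value, or the week-5 contrast from a longitudinal model that constrains the two groups to a common baseline mean. Naming one also removes the ambiguity between levels and changes.

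In the results that feed the larger trial, report the residual (adjusted) SD and the observed T0–T1 correlation for each outcome, alongside the effect estimate.

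The cost is one degree of freedom and a change of analysis wording. No extra data are needed, since T0 is already collected for every efficacy outcome.
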